## Abstract

**Background:**

Temporomandibular disorder (TMD) is a condition encompassing clinical symptoms of the temporomandibular joint, masseter muscle, and surrounding structures. Hominis placental pharmacopuncture (HPP), consisting of human placental extract, has been reported as effective for treating chronic musculoskeletal disorders, but a lack of well-designed randomised controlled trial s (RCTs) mean there is insufficient evidence to prove the efficacy of HPP.

**Methods:**

This study is a two-arm parallel, assessor-blinded, multi-centre, randomised controlled trial. We will enrol 82 chronic TMD patients from rwo Korean Medicine hospitals in Axis 1, Group I according to RDC/TMD diagnostic criteria, and randomly allocate 41 patients each to an HPP group and a physical therapy (PT) group. Treatment will be administered in 10 rounds, after which there will be four follow-up visits 6, 9, 13, and 25 weeks from baseline. The primary end point is 6 weeks after baseline, and the primary outcome is the difference in Visual Analogue Scale (VAS) score for temporomandibular pain between baseline and week 6. Secondary outcomes will be Numeric Rating Scale (NRS) scores for temporomandibular pain and discomfort, temporomandibular joint range of motion, the Korean version of Beck’s Depression Index-II (K-BDI-II), Jaw Functional Limitation Scale (JFLS), Patient Global Impression of Change (PGIC) scores, and quality of life. Using data on adverse events and cost-effectiveness in the two groups, we will perform a safety assessment and a cost-effectiveness analysis (economic assessment).

**Discussion:**

This study will assess the efficacy and safety of HPP for chronic TMD compared with PT. This RCT will provide evidence for the efficacy, safety, and economics of HPP.

**Trial registration:**

clinicaTrials.gov (NCT04087005) / Clinical Research Information Service (CRIS) (KCT0004437) / IRB (JASENG 2017–09–002-002, KHNMCOH 2019–08-002) / Ministry of Food and Drug Safety (No. 31886).

## Background

Temporomandibular disorder (TMD) encompasses clinical symptoms of the temporomandibular joint (TMJ), masseter muscle, and surrounding structures. The most common symptoms of TMD are pain in the TMJ and masseter muscle, asymmetry, and restricted motion of the TMJ, and crepitus of the TMJ; these symptoms may also be accompanied by ear pain, tinnitus, dizziness, neck pain, and headaches. Symptom onset can be mild or acute and, like patients with chronic pain in other areas, continuous pain in the TMJ is often accompanied by physical, behavioural, and psychological symptoms [1]. Over 5% of the total population is estimated to have TMD, and although TMD affects people of various ages, its prevalence is especially high among 30–40year-olds, and is reported to be three times higher in females than in males [2]. According to data from the Health Insurance Review and Assessment Service (HIRA) [3], in South Korea a total of 390,000 patients received treatment for TMD in 2017, an increase of 24% from the previous 5 years.

Diagnostic tools for TMD include the American Academy of Orofacial Pain (AAOP) criteria and the International Headache Society classification [4], but the most widely used is the research diagnostic criteria for temporomandibular disorders (RDC/TMD) [5]. RDC/TMD is a multidimensional assessment that divides TMD into muscle and joint problems (Axis 1) and psychological problems (Axis 2) via a process of diagnosis and testing for symptoms including mouth opening, range of motion (ROM), pain, and discomfort. In Axis 1, TMD is classified into group I (myofascial pain), II (disc displacements) or III (other joint conditions), while Axis 2 examines the extent of pain, and the presence and extent of accompanying neuropsychological symptoms.

Conventional treatments for TMD include medication (oral, injection), physiotherapy, and surgery [1]. Drug therapy includes oral administration of non-steroidal anti-inflammatory drugs (NSAIDs), muscle relaxants, opioids, steroids, tricyclic antidepressants, selective serotonin reuptake inhibitors (SSRIs), anxiolytics, and antispasmodic drugs. However, the use of these drugs is restricted in patients with gastrointestinal adverse effects (AEs), or who are at risk of depression or drug dependence [6, 7]. In addition, local analgesics, corticosteroids, hyaluronic acid, ketamine, and botulinum toxin are administered by injection, but there is a lack of evidence supporting the efficacy of these treatments [8]. Physical therapy (PT) is widely used to treat TMD pain and dysfunction. Heat therapy and transcutaneous electrical nerve stimulation (TENS) are used to alleviate TMJ pain, whereas neck and jaw exercise programs, postural exercises, and manipulation of the jaw, neck, and face are used to improve TMJ ROM [6, 7, 9]. Surgical treatment includes arthroscopy, arthrocentesis, arthrotomy, and TMJ reconstruction [2]. However, AEs such as deafferentation pain mean it is only considered in patients who show no response after 3–6 months of conservative treatment and experience severe disruption to their daily lives, or in patients with structural, anatomical lesions. Other treatment methods include splinting, [10] cognitive behavioural therapy, counselling, and biofeedback [6, 7].

Acupuncture is the most widely used complementary and alternative medicine treatment for TMD [7]. It has been reported to be effective for musculoskeletal disease, especially pain and dysfunction of the TMJ [6, 11]). Pharmaco-acupuncture (PA) is a novel treatment combining acupuncture with herbal medicine, in which herbal medicine extracts are injected into acupoints [12, 13]. Hominis placental pharmacopuncture (HPP), which uses human placental extract as its core component, could be used in TMD treatment, but there have yet to be any well-designed, large-scale randomised control trials (RCTs) of HPP for TMD; the current level of evidence is low because most studies have thus far been small and allowed diverse concomitant treatments.

In this study, we aim to evaluate the efficacy, safety, and economics of HPP for chronic TMD. First, we will assess the comparative effectiveness and safety of HPP by comparing pain indices, functional indices, quality of life, and AEs between HPP and conventional treatment (PT). In addition, we will compare long-term cost-effectiveness between HPP and PT to assess whether HPP is a cost-effective treatment.

## Method/Design

The protocol for this study was compiled in accordance with SPIRIT 2013 Statement (Additional file 1) [14].

### Study design and setting

This study is a two-armed, parallel, multi-centre, randomised controlled study, and will be conducted at the Jaseng Hospital of Korean Medicine and Kyung Hee University Korean Medicine Hospital at Gangdong, located in South Korea. Prior to commencement, the study protocol has been approved by the institutional review board (IRB) at each centre (JASENG 2017–09–002-002, KHNMCOH 2019–08-002) and the Ministry of Food and Drug Safety (No. 31886). In addition, the study protocol has been registered at clinicaltrials.gov (NCT04087005) and Clinical Research Information Service (CRIS) (KCT0004437), and the state of the research will be continually updated. Information about the research centres and the researchers can be found at the trial registration site.

Participants will be recruited by physician’s recommendation, posters placed in the hospitals, and adverts placed on the hospital homepages and the metro transport system. On the first visit, a researcher will explain the study to the participants and ask them to complete and submit an informed consent form (ICF). Next, an examiner will screen the participant. Participants will be enrolled according to the inclusion/exclusion criteria, will visit 15 times, and undergo surveys either through face-to-face, telephone, or online interviews, or by distribution and return. There will be 10 treatment sessions consisting of two sessions per week for 5 weeks. Thereafter, there will be follow-up visits at 6, 9, 13, and 25 weeks from baseline. On the second visit, participants will be randomly allocated to either the HPP group or the PT group and receive the corresponding treatment. All participant management and treatment processes will be performed according to the protocol. To check compliance, we will verify whether participants adhere to the treatment schedule specified in the protocol. For the HPP group, compliance will be assessed by checking the frequency and schedule of procedures; for the PT group, compliance will be assessed by checking the frequency and schedule of TENS procedures. A study flow chart is shown in Fig. 1.

**Fig. 1 Fig1:**
[figure not shown]
Flow chart. *EQ-5D-5 L* EuroQol-5 Dimensions 5 Levels; *JFLS* Jaw Functional Limitation Scale; *K-BDI-II* Korean-Beck Depression Inventory-II; *HPP* hominis placental pharmacopuncture; *NRS* Numeric Rating Scale; *PGIC* Patient Global Impression of Change; *PT* Physical therapy; *SF-12* Short Form Health Survey 12; *TMJ ROM* range of motion of temporomandibular joint; *VAS* Visual Analogue Scale

### Inclusion/exclusion criteria

#### Inclusion criteria

Patients with unilateral or bilateral TMJ painPatients with Visual Analogue Scale (VAS) ≥ 40 mm for the area showing TMJ pain (for patients with bilateral pain, the side with worse pain)Patients complaining of persistent of sporadic TMJ pain for at least 3 monthsPatients diagnosed as myofascial TMD (Axis I: Group 1) based on the RDC/TMD diagnostic criteria [5]Patients aged 19–70 years on the date they sign the consent formPatients who provide consent to participate in the trial and return the ICF

#### Exclusion criteria

Patients whose current pain episode developed or worsened because of a road traffic accident or traumatic injuryPatients diagnosed in Group 2 or 3 of Axis I based on the RDC/TMD diagnostic criteriaPatients who have undergone surgery related to the TMJPatients with other chronic diseases that could interfere with interpretation of the treatment effects or outcomes (e.g. rheumatoid arthritis, neoplastic disease, stroke, or myocardial infarction)Patients currently taking steroids, immunosuppressants, psychiatric drugs, or other drugs that could affect the study resultsPatients who have received HPP within the last month, or who have taken drugs that could affect pain, such as NSAIDs, within the last weekPregnant or breastfeeding womenPatients who have finished participation in another clinical trial within the last month, who participated in another trial within 6 months of selection, or who are planning to participate in another clinical trial during the follow-up periodPatients with a history of hypersensitivity after HPPDiabetic patients with uncontrolled blood glucose (fasting blood glucose ≥180 mg/dl)Patients with aspartate aminotransferase or alanine aminotransferase at least two times the normal range at the testing centrePatients with creatinine at least two times the normal range at the testing centrePatients suspected to have organic diseasePatients with cardiac, hepatic, renal, or other serious complicationsPatients with psychogenic diseasePatients who are unable to receive pharmacopuncture due to, e.g. inflammation or a wound at the relevant acupointsOther situations when patients whose participation in the trial is judged by a researcher to be problematic

### Randomisation and allocation concealment

An independent statistics expert will use nQuery Advisior 7.0 (or SAS 9.0 [SAS Institute Inc., Cary, NC, USA] or SPSS 21.0 [IBM Corp., Armonk, NY, USA]) to allocate participants into each group by block randomisation in a 1:1 ratio (41 persons/group). The results of random allocation will be sealed, such that they cannot be seen from outside, and sent to each centre, where they will be managed in a double-locked container. Before treatment, a random envelope will be opened in front of the enrolled participant, the random allocation numbers assigned to each group will be recorded in an electronic chart, and no changes will be allowed after allocation. Participant enrolment at each centre will proceed by competitive enrolment.

### Blinding

Because this study does not allow the participant or treatment provider to be blinded to their group, we will use a single-blinded design, where only the assessors are blinded. Participants will be assessed away from the treatment area, by an investigator who did not participate in treatment procedures and is blinded to the treatment group; efforts will be made to prevent the investigator from knowing the allocated group. The data analyst will not be blinded to two groups. The design is open label with only the outcome assessor being blinded, so unblinding will not occur in this study.

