### Sample size

This is an investigator-initiated clinical trial, and we have calculated the required sample size with reference to similar studies and our clinical experience. First, we set a significance level of α = 0.05 (two-tailed tests), a type 2 error (β) of 0.2, and a test power of 80%. Because there are no previous studies comparing pharmacopuncture with PT for the TMJ, we selected a moderate-to-high effect size for the comparison of mean VAS between the two groups based on our clinical experience, and used Cohen’s d = 0.65 [36]. Using these parameters, we calculated the sample size using G*Power 3.1.7. Based on an effect size = 0.65, the required sample size was estimated to be 39 persons/group (total 78 persons). However, as we plan to use an analysis of covariance (ANCOVA) correcting for the outcome at baseline for our main analysis, we calculated the sample size assuming the correlation between baseline and primary endpoint to be 0.4 [(1–0.4*0.4)*78], and found that the minimum required number of participants was a total of 65 persons [37]. Thus, to account for a dropout rate of 20%, we calculated that the number of participants we need to recruit is a total of 82 persons (41 persons/group).

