### Statistical analysis

As an RCT of chronic TMD patients, this study will compare the difference within and between groups for data on efficacy, safety, and economics. The main analysis will be the ITT analysis, and a PP analysis will also be performed. The demographic results, such as sex, age, occupation, and disease history, and the treatment expectancy will be assessed by group; continuous variables will be presented as the mean ± standard deviation (SD) and categorical variables will be presented as n (%). Differences will be tested using chi-square tests and independent *t* tests. Efficacy outcomes are the changes in continuous outcomes (VAS, NRS, K-BDI, JFLS, EQ5D-5 L, SF-12) at each time point relative to baseline. The primary outcome is the change in VAS from baseline to the primary end point (week 6) in each group. For safety outcomes, we will compare the incidence of AEs between groups; after graphing all the reported ARs in participants who have received treatment at least once, we will calculate the proportion of patients who have experienced AEs in each group, and compare these using chi-square tests and Fisher’s exact test. To compare the HPP and usual care groups, for continuous variables, we will perform an ANCOVA adjusted for the baseline outcome. For categorical variables, we will use chi-square tests of Fisher’s exact test, and to analyse within-group differences between time points, we will use paired *t* tests. Additionally, we will perform an ANCOVA adjusted for baseline outcomes and covariant factors that show a statistically significant difference between the treatment groups at baseline, and we will perform a repeated measures analysis of variance (RM ANOVA) to test differences in the changes across each visit. We will perform subgroup analyses according to RDC/TMD diagnosis (Group Ia, Ib), mouth opening, and K-BDI score. Missing values will be handled in a blinded state, mainly using multiple imputation (MI), last observation carried forward (LOCF) will additionally be used, and sensitivity analyses will be performed. All statistical analysis will be performed using SAS version 9.4 statistical package (SAS Institute, Cary, NC, USA), and statistical significance will be defined as *p* < 0.05.

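### The protocol leaves the data analyst unblinded yet promises blinded handling of missing values, and names no person or masked step that would reconcile the two

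*Protocol article*

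**What the plan says.** The Blinding section explains that participants and treatment providers cannot be blinded, so only the assessors are. It then says of the analyst: "The data analyst will not be blinded to two groups". It closes: "The design is open label with only the outcome assessor being blinded, so unblinding will not occur in this study".

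The Statistical analysis section says: "Missing values will be handled in a blinded state, mainly using multiple imputation (MI), last observation carried forward (LOCF) will additionally be used". The sentence is passive. It does not say who does the work, what that person is blinded to, or until when.

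The main analysis is otherwise specified. On analysis sets: "The main analysis will be the ITT analysis, and a PP analysis will also be performed". On the model, the Statistical analysis section says "for continuous variables, we will perform an ANCOVA adjusted for the baseline outcome", and the Sample size section confirms it: "as we plan to use an analysis of covariance (ANCOVA) correcting for the outcome at baseline for our main analysis". A further ANCOVA, introduced as an addition, also adjusts for "covariant factors that show a statistically significant difference between the treatment groups at baseline".

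Two other sections touch on access. Randomisation and allocation concealment gives an independent statistics expert the task of generating the allocation. Data collection and management closes the data, after cross-checking, to every investigator except the data coordinator. Neither section describes a blinded analysis step.

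**The concern.** Imputation is normally part of the analysis. If the analyst knows the arms and nobody but the assessor is blinded, the protocol identifies no one who could carry out the promised blinded step.

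The promise matters more here than in a fully masked trial. The primary outcome is a pain VAS marked by patients who know their treatment, so blinding the assessor protects it only in part. Blinded handling of missing data is one of the few safeguards left, and the Blinding section undercuts it.

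The wording carries a second risk. Blinded handling could be taken to mean imputing without the treatment variable. That is a different procedure from imputing with coded arms, and it would bias the comparison towards no difference.

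**Working it through.** **1. The statements side by side**

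| Question | Blinding section | Statistical analysis section |
|---|---|---|
| Who is blinded? | The outcome assessor only | Whoever handles missing values (not named) |
| Is the analyst blinded? | No | Not stated; the missing-data step is said to be blind |
| Is there a masked code or a second statistician? | None described | None described |

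Both statements could stand if a separate blinded person did the imputation, or if arms were masked for that step. The document describes neither, and limiting blinding to the assessor counts against both. This is a conflict as described, not a logical impossibility.

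**2. Which choices are still open**

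| Step | Status in the protocol | Bears on the main comparison? |
|---|---|---|
| Analysis set | ITT is main; PP is additional | Fixed |
| Model | ANCOVA adjusted for baseline | Fixed |
| Missing-data method | MI is main; LOCF is additional | Method fixed; imputation details not given here |
| Covariates from baseline tests | Additional ANCOVA | No |
| PP membership | Additional analysis | No |
| Subgroup cuts | Subgroup analyses | No |

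Only the imputation details reach the main comparison. They may be set in an analysis plan that is not shown. The covariate screen is a significance rule: arms labelled A and B give the same p values and pick the same covariates, so blinding does not change it.

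**3. How many patients could be affected**

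Inputs from the Sample size section: d = 0.65, two-sided α = 0.05, 80% power, baseline-to-endpoint correlation 0.4, dropout 20%.

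- Two-sample t test, noncentral t: power is 0.799 at 38 per group and 0.809 at 39 per group. This gives 39 per group, 78 in total, as stated.
- ANCOVA factor: (1 − 0.4²) × 78 = 0.84 × 78 = 65.52, stated as 65.
- Dropout: 65 / 0.8 = 81.25 and 65.52 / 0.8 = 81.9. Both round up to 82, as stated.
- Patients possibly needing imputation: 0.20 × 82 = 16.4, about 16.

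The sample size reproduces and does not depend on this point. It is used only for scale.

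**4. Why the meaning of blinded needs stating**

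If arm is left out of the imputation model, imputed patients carry no treatment difference. With 20% missing completely at random, the expected effect is about 0.80 × 0.65 = 0.52 SD.

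A simulation under assumed conditions agrees (82 patients, correlation 0.4, 20% dropout completely at random, 10 imputations, 3,000 runs):

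| Imputation model | Mean estimate for a true 0.65 SD effect | Power |
|---|---|---|
| Arm included | 0.65 | about 79% |
| Arm omitted | 0.52 | about 61% |

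The protocol does not say that arm will be omitted. The figures show only what that reading would cost.

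**The case against.** The case on the other side is substantial.

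- **No actor is named.** The missing-data sentence does not say that the analyst does the imputing. A separate person or a masked step would let both statements stand. This is right, and it rules out calling the two irreconcilable. It does not remove the need to say which arrangement is meant.
- **An unblinded analyst is openly disclosed in an assessor-blinded, otherwise open-label trial.** This stands. It is a legitimate arrangement if choices are fixed before data access. The defect is promising a blinding for which no arrangement is described.
- **The primary analysis is already fixed.** This stands too. A reader might infer that the choices determining the primary result will be made with arms known. The document does not support that: set, model and main method are stated, MI ranks above LOCF, and the remaining details may be in an analysis plan that is not shown.
- **Simulated error rates overstate the exposure.** Under the assumptions above, plus an earlier value correlated 0.4 with the endpoint given baseline and a pure-noise covariate, a fixed MI ANCOVA has a type I error of about 5.0%. Reporting the better of MI and LOCF gives about 7.6%, and the best of four analyses about 8.4%. A reader might take these as the expected inflation. They assume picking the smallest p value, which the protocol's ranking of analyses does not permit for the main result.
- **Masking is harder than recoding one variable.** This stands. Compliance is checked through arm-specific procedures (Study design and setting), and adverse event data may reveal the arm. The fix has to deal with both.

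**Conclusion.** The point holds as an inconsistency that should be resolved. The Blinding section leaves the analyst unblinded and limits blinding to the assessor; the Statistical analysis section promises a blinded missing-data step; nothing in the document joins the two.

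The consequence is modest. Imputation details, PP membership and subgroup cuts could influence the reported results if settled with arms known. The protocol gives no basis for saying that they will be, or that the primary result is compromised. No bias can be calculated from the document. The only scale available is the planned dropout allowance, about 16 of 82 patients, which assumes that dropout turns into missing week-6 VAS values.

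A change is still worth making: the outcome is self-reported by unblinded patients, and the remedy is cheap. The conclusion rests on the article as shown. A full protocol or analysis plan may already name a blinded person, in which case aligning the wording would be enough.

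**What to change.** **Blinding section.** Replace the statement on the analyst with text to this effect: the trial statistician receives data with arms coded A and B; the analysis sets, the imputation model, and the primary and sensitivity analyses are completed and signed off before the code is broken.

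**Custody of the code.** The independent statistics expert who generates the allocation alone holds the key linking A and B to the treatments, and is not the person who runs the analysis. The data coordinator should not hold it: under Data collection and management that role alone keeps access to the data, so key and data would sit together.

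**Statistical analysis section.** State who handles missing values, that blinded means working with coded arms until sign-off, and that coded arm stays in the imputation model as a predictor.

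**Arm-revealing data.** Withhold adverse event listings until after sign-off. Reduce HPP- or TENS-specific compliance records to a neutral count of sessions attended, so that PP membership can be settled blind.

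**Cost.** One recoded variable, a derived attendance count, a sign-off step and a short delay in releasing some safety listings to the statistician. Sample size, visits and trial procedures do not change.
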